### Study procedure

After signing the consent form, participants will complete a 20-minute baseline survey. Upon completion of the baseline survey, all participants will receive a $25 gift card and be randomized to the intervention (*n* = 50) or the waitlist control condition (*n* = 50). We will utilize stratified randomization to ensure that an equal number of males and females are randomized into each condition. Those randomized into the intervention will be prompted by research personnel to complete the 30-minute intervention, which will be delivered via a webpage accessible through a mobile device. More specifically, participants will be emailed a web link to access the intervention along with personalized log-in information consisting of their email address and a unique 4-digit PIN code. We will collect backend data indicating whether participants have completed all intervention components. We anticipate that most or all participants will complete the intervention given the 100% completion rate in one sitting among those who beta tested our program (completed June 2024; *N* = 20). However, if there are participants who have not completed the full intervention within 24 h of being given access to the program, research personnel will send a text and email reminder. All participants will then complete brief surveys, which will include the same measures from the baseline survey, 2, 4-, and 8-weeks post-randomization (see Fig. 1), to determine the efficacy of the program on reducing vaping and susceptibility to smoking in the immediate term (2-weeks post-randomization) and short term (4- and 8-weeks post-randomization). At most, three text messages and three emails will be sent to remind participants to complete the assessments. Those who do not respond despite the reminder attempts are counted as dropout at each time point. However, participants who do not respond in the previous assessment waves will still be contacted for later assessments. For instance, a participant who did not complete the 2-week follow-up assessment will still be asked to complete the 4-week assessment. Participants will receive a $25 Amazon gift card for completing each survey (up to $100 total). Participants will also be offered raffle tickets for a chance to win various prizes (e.g., movie tickets, $50 Amazon gift card). More specifically, participants will receive one raffle ticket for each survey they complete within two days of receiving the survey via email, giving them the opportunity to earn up to four raffle tickets. Participants who complete all four surveys within two days of receiving them will earn an additional three raffle tickets.

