### Control group

Participants randomized into the control condition will be instructed to complete the same online surveys (baseline, 2-,4-, and 8-week surveys) sent via email. Control participants will be given the option to access the intervention upon completion of their final assessment at 8-weeks. Along with participants in the experimental group, they will also receive a list of national and local resources for information about the effects of vaping in young people and help with reducing vaping behaviors after completion of the final assessment.

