#### Primary outcomes

Our primary outcomes are reductions in past 7-day self-reported vaping frequency (i.e., the number of days they vaped, the number of times per day they picked up their device to vape, and the number of puffs taken before putting their device away per day in the past 7 days), biochemically verified 7-day point prevalence abstinence, and smoking susceptibility using the 4-item Expanded Susceptibility to Smoking Index [35]. At each follow-up assessment, participants who report 7-day abstinence will be mailed a saliva cotinine test kit to provide biochemical verification of their abstinence. Participants will be provided with written instruction on how to perform the saliva cotinine test but will also be contacted by a research team member via a Zoom video call during verification to ensure that participants are able to correctly complete the test. Results will be provided immediately via the test strip and shown to the research team member to verify. Those with a cotinine level of < 30 ng/ml will be reported as having achieved biochemically verified nicotine vaping abstinence. Participants who complete this cotinine test will be compensated with a $20 Amazon gift card.

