### Data analysis plan

#### Primary analysis

Treatment effects of the intervention will be examined using within-subjects repeated measures analysis of variance (RM-ANOVA), which allows for investigations of changes in mean scores over 3 or more time points. Specifically, we will evaluate two models to examine whether there were changes in past 7-day vaping frequency and smoking susceptibility across 3 time points (2-, 4-, and 8-weeks post-randomization) among those who completed the intervention. Logistic regression will be used to examine point prevalence abstinence at our 3 follow-up timepoints. Next, RM-ANOVA will be used to determine whether any changes in past 7-day vaping frequency and smoking susceptibility are the result of the interaction between the condition and time. Past 7-day point prevalence abstinence will be compared between the treatment and control groups using logistic regression. To handle missing data, we will conduct an intent-to-treat (ITT) analysis in which those who were lost to follow-up will be marked as treatment failures.

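### The plan's one missing-data rule, lost to follow-up equals treatment failure, gives no value for the vaping-frequency and susceptibility scores, so their RM-ANOVA would by default be complete-case despite the ITT label

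*Protocol article*

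**What the plan says.** All references are to the protocol article.

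- **Outcomes (Primary outcomes).** There are three. Vaping frequency over the past 7 days is a set of counts, including "the number of days they vaped, the number of times per day they picked up their device to vape" and puffs. The second is "smoking susceptibility using the 4-item Expanded Susceptibility to Smoking Index". The third, biochemically verified 7-day abstinence, is the only one with a success/failure scale.
- **Models (Primary analysis).** For the first two outcomes, "RM-ANOVA will be used to determine whether any changes in past 7-day vaping frequency and smoking susceptibility are the result of the interaction" between condition and time. For the third, "Past 7-day point prevalence abstinence will be compared between the treatment and control groups using logistic regression".
- **Missing data (Primary analysis).** The section closes with one rule: "we will conduct an intent-to-treat (ITT) analysis in which those who were lost to follow-up will be marked as treatment failures". It names no outcome.
- **Follow-up (Study procedure).** Dropout is counted separately at each time point, and "participants who do not respond in the previous assessment waves will still be contacted for later assessments". Participants with some waves missing and later ones observed are therefore expected.

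**The concern.** A participant lost to follow-up can be scored as a failure on abstinence by coding not abstinent. For days vaped, pick-ups, puffs or a susceptibility score, the rule gives no number to enter. RM-ANOVA in its standard form needs a value at every wave, so with nothing entered a participant who misses week 2 but returns at weeks 4 and 8 is dropped altogether.

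Two things are at stake. The main one is selection: those who answer every survey are a group formed after randomisation, so the comparison is no longer between the arms as randomised. The second is power, because every partly observed participant is lost, although the trial keeps contacting them and pays for each completed survey.

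**Working it through.** **1. Does the rule fit the models?**

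| Primary outcome | Scale | Model | Value implied by treatment failure |
|---|---|---|---|
| Verified abstinence | yes/no | logistic regression | not abstinent |
| Vaping frequency | counts | RM-ANOVA | none stated |
| Smoking susceptibility | 4-item index | RM-ANOVA | none stated |

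The rule works for one outcome of three.

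**2. The plan's own power figures.** The Power analysis section gives power 0.8, alpha 0.05, and required totals of 62, 24 and 10 for f = 0.15, 0.25 and 0.45. For the group-by-time interaction with k = 2 groups, m measurements and correlation ρ:

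- λ = f² × N × m / (1 − ρ)
- df1 = (k − 1)(m − 1), df2 = (N − k)(m − 1)
- power = P(F′(df1, df2, λ) > F₀.₉₅(df1, df2)), where F′ is noncentral F

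The article states neither ρ nor a sphericity correction; ρ = 0.5 and none are assumed. With m = 4 the required totals are 62, 24 and 10, exactly as stated. With m = 3 they are 74, 28 and 10. The stated totals thus match four measurements, while the analysis text speaks of "across 3 time points (2-, 4-, and 8-weeks post-randomization) among those who completed the intervention". Both are carried forward. The calculation assumes complete data.

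With all 100 complete and f = 0.15 (f² = 0.0225):

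- m = 4: λ = 0.0225 × 100 × 4 / 0.5 = 18.0, df 3 and 294, power 0.96
- m = 3: λ = 0.0225 × 100 × 3 / 0.5 = 13.5, df 2 and 196, power 0.91

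**3. How many remain complete?** No dropout rate is given, so a range is assumed. Randomisation follows completion of the baseline survey, so only the three follow-ups can be missing, whether or not baseline enters the model. If each is missed independently with probability q, the complete fraction is (1 − q)³ and the fraction with at least one follow-up is 1 − q³:

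- q = 0.10: 0.9³ = 0.729; 1 − 0.001 = 0.999
- q = 0.15: 0.85³ = 0.614; 1 − 0.003 = 0.997
- q = 0.20: 0.8³ = 0.512; 1 − 0.008 = 0.992

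More than 99% would have usable follow-up data in each case. If instead the same people miss every wave, the complete fraction is 1 − q.

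**4. Power at f = 0.15 in the complete cases (ρ = 0.5)**

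| Assumed missingness | N complete | λ (m = 4) | Power, m = 4 | λ (m = 3) | Power, m = 3 |
|---|---|---|---|---|---|
| none | 100 | 18.00 | 0.96 | 13.50 | 0.91 |
| 10% per wave, independent | 73 | 13.14 | 0.87 | 9.86 | 0.80 |
| 15% per wave, independent | 61 | 10.98 | 0.79 | 8.24 | 0.72 |
| 20% per wave, independent | 51 | 9.18 | 0.71 | 6.89 | 0.63 |
| same 15% miss every wave | 85 | 15.30 | 0.92 | 11.48 | 0.86 |

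Power drops below 0.80 at about 15% independent missingness per wave with four measurements, and at about 10% with three.

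**The case against.** **The rule may be meant for abstinence only.** It directly follows the sentence on logistic regression of abstinence. On that reading it is coherent, and the article is merely silent on the other two outcomes, which a condensed article may leave to a fuller plan. The reading is possible. But the sentence is introduced as the way missing data will be handled, names no outcome, and carries the ITT claim for the whole primary analysis. The article also fixes RM-ANOVA, so the method and the ITT label sit together in the text and do not match.

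**A reader might infer that the rule cannot be applied to the scores at all.** That goes too far. The aim is reduction and baseline values are collected, so failure could be defined as no change from baseline. If such values were entered, nothing would be missing and RM-ANOVA would drop nobody. No such value is stated, however, and it would be a single imputation whose assumption the plan does not test. The complete-case result is therefore what happens by default; the article does not announce it.

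**A reader might also infer that dropout will differ by arm,** because "Control participants will be given the option to access the intervention upon completion of their final assessment at 8-weeks", which gives only controls that reward for finishing. The documents do not support a forecast. Both arms are paid $25 for each survey, can earn raffle tickets and receive the resource list after the last assessment. The control arm's extra is attached to week 8 and does not bear directly on weeks 2 and 4. Unequal dropout is possible, but its size and direction are unknown.

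**Independent misses are pessimistic.** This stands. The clustered row of the table shows a much smaller loss of power, and the reminders and payments may keep missingness low.

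**Conclusion.** The point holds for vaping frequency and smoking susceptibility, not for abstinence, where the rule is usable. Followed as written, and with no value imputed, the plan does not deliver its ITT claim for two of its three primary outcomes, and it discards follow-ups that it sets out to collect.

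The power cost depends on assumptions the article does not supply: the missingness rate, its pattern across waves, and ρ = 0.5. Within the range shown, power at f = 0.15 lies between 0.71 and 0.92 with four measurements, against 0.96 with complete data, and between 0.63 and 0.86 with three, against 0.91. With clustered dropout the power loss is modest. The selection problem remains under either pattern, and it is the stronger reason to change the plan.

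**What to change.** 1. Analyse vaping frequency and susceptibility with a likelihood-based mixed model, or its count-data equivalent for the counts. Use every available follow-up of every randomised participant and include the baseline value.
2. Restrict the missing-equals-failure rule to verified abstinence and apply it wave by wave, so that a participant who returns is scored on the returned data.
3. Add one sensitivity analysis for abstinence under a different missing-data assumption, for example multiple imputation by arm using baseline vaping and the observed waves.

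The cost is a change of wording, slightly more programming and one extra result to report. Visits, sample size and participant burden do not change. The wording should be fixed before outcome data by arm are seen, so that the missing-data method is not chosen with the results in view.

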#### Secondary analysis

Secondary outcomes will also be analyzed using RM-ANOVA. Specifically, treatment effects will be examined by evaluating changes in perceived harms of vaping and smoking, motivation to vape and smoke, quitting vaping self-efficacy, and vaping quit attempts. We will also evaluate whether, compared to controls, participants in the experimental group will report greater perceptions of harms of vaping and smoking, quitting vaping self-efficacy, and vaping quit attempts, and lower levels of motivation to vape and smoke at each follow-up.

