**Methods:**

A 2-arm pilot randomized controlled trial (RCT) will be conducted by recruiting young adults ages 18–24 who reported vaping at least once per week in the past 30 days and having never smoked cigarettes at baseline. Participants will be recruited via social media ads and be randomly assigned to an intervention arm, which will be the Live Free From E-cigarettes (LIFFE) mobile-based program (*n* = 50), or a waitlist control arm (*n* = 50). The primary outcomes are biochemically verified 7-day point prevalence abstinence for nicotine vaping, vaping reduction, and smoking susceptibility. Outcomes are measured at 2-, 4-, and 8-weeks after randomization.

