#### Baseline variables

The baseline survey will include an assessment of our primary and secondary outcomes (described further under Primary and Secondary Outcomes), which include e-cigarette use (e.g., past month use, days of use within the past 7 days), smoking susceptibility, perceptions of vaping- and smoking-related norms, and perceptions of vaping- and smoking-related harms. Further, we will assess for past year vaping quit attempts, motivation to quit vaping, quitting vaping self-efficacy, e-cigarette dependence, and the use of vaping harm reduction strategies. E-cigarette dependence will be measured with the E-cigarette Dependence Scale [33] and the use of vaping harm reduction strategies will be measured with the Vaping Protective Behavioral Strategies Scale [34].

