#### Secondary outcomes

Secondary outcomes for this study are perceived harms of vaping measured using the Short Form Vaping Consequences Questionnaire [36], perceived harms of smoking measured with the Short Form Smoking Consequences Questionnaire [37], motivation to vape (i.e., plan to stop, decrease, continue, or increase vaping), motivation to initiate smoking, and quitting vaping self-efficacy (i.e., 5-point scale assessing confidence about quitting vaping “someday” and “in the next 6 months”). After this study had already been registered to clinicaltrials.gov, we decided to include vaping quit attempts as a secondary outcome based on the current literature [17, 20]. We will measure vaping quit attempts by asking participants whether they have made a quit attempt since their last assessment (yes/no) and to indicate the number of attempts they have made since their last assessment.

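### Quit attempts are counted over 2-, 2- and 4-week recall windows but analysed by RM-ANOVA as one repeated measure, so window length alone produces a change over time

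*Protocol article*

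**What the plan says.** Secondary outcomes, in the protocol article, measures quit attempts by "asking participants whether they have made a quit attempt since their last assessment (yes/no) and to indicate the number of attempts" made over that same period. The abstract's Methods give the schedule: "Outcomes are measured at 2-, 4-, and 8-weeks after randomization". Study procedure adds that "participants who do not respond in the previous assessment waves will still be contacted for later assessments".

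Secondary analysis then fixes the method for the whole group of outcomes: "Secondary outcomes will also be analyzed using RM-ANOVA". It says that "treatment effects will be examined by evaluating changes in perceived harms of vaping and smoking", and the same list goes on to name quit attempts. It also plans a comparison with controls at each follow-up. It states no rate scaling and no exposure offset, and it gives no separate model for a binary or count outcome. Primary analysis, by contrast, uses logistic regression for the binary abstinence outcome.

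At baseline the question covers a different period: "we will assess for past year vaping quit attempts".

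**The concern.** RM-ANOVA compares means across waves as if each wave measured the same quantity. Here it does not: the week-8 question covers about twice as much time as the week-2 or week-4 question. A rise at week 8 mixes behaviour with questionnaire design, and the plan has no step that separates them.

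Two readings of the results are at stake. A rise within the intervention arm could be reported as a response to the programme. The Limitations section also says the team will report whether and when effects fade over the 8 weeks; for quit attempts, the longer last window works against seeing a fade.

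**Working it through.** **Inputs from the article.** Surveys at weeks 2, 4 and 8; attempts recalled since the last assessment; 50 participants per arm, 100 in all; alpha 0.05. Primary analysis runs its within-subject models on intervention completers (at most 50 people) over the three follow-ups, and Secondary analysis says it will also use RM-ANOVA.

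**Assumed inputs.** The article gives no quit-attempt rate, so there is no figure of its own to reproduce here. Assumed: a constant 0.1 to 0.2 attempts per person-week, with gamma spread between people (shape 1).

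**Step 1: windows.** Week 2: 2 − 0 = 2 weeks. Week 4: 4 − 2 = 2 weeks. Week 8: 8 − 4 = 4 weeks. After a missed week 2, the week-4 window is 4 weeks. At week 8 it is 6 weeks if only week 4 was missed, and 8 weeks if both were.

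**Step 2: expected count = rate × window.**
- 0.1 per week: 0.2, 0.2, 0.4.
- 0.2 per week: 0.4, 0.4, 0.8.

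The count doubles at week 8 at any constant rate.

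**Step 3: chance of any attempt.** With one common rate it is 1 − exp(−rate × window). At 0.1 per week: 1 − exp(−0.2) = 18%, then 1 − exp(−0.4) = 33%. With the gamma spread used in the simulation it is 1 − 1/(1 + rate × window): 1 − 1/1.2 = 17%, then 1 − 1/1.4 = 29%.

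**Step 4: simulated RM-ANOVA.** Gamma-Poisson counts, complete follow-up, constant rate, no arm difference, thousands of trials per setting. Share of trials with p < 0.05 for time (approximate):

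| Setting | Count | Yes/no |
|---|---|---|
| One arm of 50, 0.1 per week | 44% | 36% |
| One arm of 50, 0.2 per week | 74% | 49% |
| All 100 pooled, 0.1 per week | 75% | 62% |
| All 100 pooled, 0.2 per week | 97% | 82% |
| Equal 2/2/2 windows, any of these | 5% | 5% |

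The last row shows that the unequal windows cause the excess; the non-normal data do not.

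**Step 5: condition-by-time test.** With no arm difference it rejects in about 5% of trials, so it keeps its level. Now let the intervention double the rate throughout. With control at 0.1 per week, control means are 0.2, 0.2, 0.4 and intervention means 0.4, 0.4, 0.8. The difference is 0.2, 0.2, 0.4, which grows at week 8 although the rate ratio stays at 2. The count interaction is then significant in about 10–30% of trials over control rates of roughly 0.05 to 0.2 per week, against about 5% with equal windows. The yes/no interaction stays close to nominal (about 5–8%).

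**Step 6: a hidden fade.** If the rate is 0.1 per week to week 4 and 0.05 after it, expected counts are 2 × 0.1 = 0.2, 2 × 0.1 = 0.2 and 4 × 0.05 = 0.2. A halving of the rate looks like no change.

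**The case against.** The strongest reply is that this is a randomised trial, and both arms face the same window at a given wave. That stands. With complete follow-up the arm comparison at each wave is not biased, and the condition-by-time test keeps its level when the arms do not differ. A reader might take the rejection rates in the table as the error rate for the treatment effect; they apply to the time effect only. The pooled figures also need 100 people in the model, whereas the within-subject model described under Primary analysis has at most 50.

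Three further readings are tempting, but the article does not support them.

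- **The past-year baseline item enters the RM-ANOVA.** Primary analysis names only the three follow-ups as time points, and Baseline variables lists past-year attempts apart from the outcome measures. Its entry would be inference.
- **Missed waves distort the arm comparison.** This needs the arms to skip waves at different rates, and the article gives no such rates. A complete-case RM-ANOVA would drop these participants; the longer windows would matter in the comparisons at each follow-up. It is a possibility, not a demonstrated bias.
- **The motivation item has the same fault.** It is "motivation to vape (i.e., plan to stop, decrease, continue, or increase vaping", a current plan with no recall window. Treating it as a mean score is a modelling preference and is not part of this point.

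It is also fair that quit attempts are one secondary outcome, added after registration, in a pilot of 100. That limits the weight of the point. It does not remove it, because the article states both the recall period and the method and does not leave them to a later plan.

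**Conclusion.** The point holds for quit attempts and for change over time. As written, the analysis confounds time with recall length. The doubling of the expected count at week 8 follows from the schedule at any constant rate. The size of the false time effect (about 44–74% for the count and 36–49% for yes/no in one arm of 50) rests on the assumed rates, the gamma spread and complete follow-up. If the intervention has a real and constant effect on the rate, the count interaction can be misread as a growing effect; a real fade can be masked. No primary outcome uses this recall window. The change should be made before analysis, at moderate priority.

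**What to change.** Replace RM-ANOVA for quit attempts in the Secondary analysis section.

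- **Number of attempts:** a Poisson or negative binomial model with log(weeks since last completed assessment) as offset, using each person's own window, with arm, time and arm-by-time terms. Each person contributes up to three counts, so use GEE or a random person effect; without one, the standard errors could be wrong.
- **Yes/no item:** a binary model that accounts for window length, for example complementary log-log with the same offset, again allowing for repeated answers. Alternatively, analyse any attempt by week 8 with logistic regression by arm, and state how people without a week-8 survey are handled.
- **Past-year attempts at baseline:** use as a covariate only, not as a time point.

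The cost is revised wording and a little more programming. No new data are needed: the windows come from survey completion dates, which the study must already track because raffle tickets depend on completing a survey within two days.
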